#### Summary of baseline data and flow of participants

Descriptive statistics will be used to summarise characteristics of patients and compare baseline characteristics between groups. Means and SDs will be used for continuous outcomes or medians and interquartile ranges if required for skewed data. Categorical variables will be summarised using frequencies and proportions. Baseline variables to be explored include those described in the ‘Plans for assessment and collection of outcomes {18a}’ section. Patient-reported outcome scores based on standardised questionnaires will be calculated based on the developers’ scoring manuals and missing erroneous items will be handled according to these manuals.

Secondary analyses will adjust for any prognostic variables showing a marked imbalance at baseline (ascertained using descriptive statistics).

#### Primary outcome analysis

The PROM, ICIQ-UI-SF at 1 year post-randomisation is the primary outcome. Comparisons between treatment arms will be made using a multivariable linear model with random effect for site to account for within-site correlation. The model will adjust for baseline ICIQ-UI-SF scores. The underlying assumptions of the model will be checked, and analyses adjusted accordingly.

#### Secondary outcome analysis

The secondary outcomes in this study explore the longer-term impacts of the intervention on self-reported and objective improvements in continence and sexual function. Continuous measures will be studied in the same manner as the primary outcome and ordered categorical variables will be studied using ordinal logistic regression. Where outcomes are measured at multiple time points post-randomisation repeated measures analyses will be used to examine whether treatment effects are sustained, diminished or emerged later. These will be investigated formally by introducing an interaction term between treatment arm and time. All models will adjust for the outcome at baseline.

Surgical outcomes will be described using descriptive statistics for those women allocated to the surgical arm and no formal comparisons will be made between surgeries.

### Interim analyses {21b}

Women will complete outcome measures at 6 months and 1, 2 and 3 years after randomisation. Analyses of the 6-month to 3-year follow-up data will be completed at the same time, as the 2- and 3-year follow-up data provides context for the primary outcome data at 1 year. An independent DMC will review confidential accumulating data at its discretion, but at least annually. No interim statistical analyses by study arm are planned.

### Methods for additional analyses (e.g. subgroup analyses) {20b}

#### Subgroup analyses

We will conduct a small number of pre-defined subgroup analyses to assess whether the difference in ICIQ-UI-SF at 1 year between the two treatment arms differed according to baseline characteristics including age. Effect modification will be assessed by including an interaction term in the regression model and formal tests of interaction will be performed. These analyses will be outlined in detail in the SAP which will be agreed in advance by the TSC and DMC.

#### Adjusted analysis

All primary analyses will adjust for the outcome as measured at baseline. Secondary analyses will adjust for any prognostic variables demonstrating marked imbalance at baseline as determined using descriptive statistics.

#### Health economic evaluation

The base case cost-effectiveness analyses will be from an NHS perspective, comparing costs in relation to QALYs at 1-year follow-up. A societal perspective analysis at 1 year and a further NHS secondary care perspective analysis at 3 years, comparing costs in relation to QALYs, will also be conducted. Discounting for the 3-year analysis will be based on NICE recommended rates at the time, currently 3.5% for both costs and benefits. The relevant most up-to-date NHS reference costs will be used to value the information obtained from either the Hospitals’ costing systems or HES. Community-based NHS resource use, time off work and normal activities will be valued using routine data, e.g. Unit Costs of Health and Social Care; ONS Annual Survey of Hours and Earnings. Participant car travel will be valued using HMRC advisory fuel rates. All other travel costs and out of pocket expenditure will be valued as reported by the participants.

The EQ-5D-5L will be administered at baseline, 6 months and 1, 2 and 3 years after randomisation. These values will be transformed into utility scores using the recommended value set at the time of analysis, and individual QALYs will be calculated using the area under the curve approach.

At both 1-year and 3-year time points and for all perspectives, differences in mean costs and QALYs between the trial arms will be evaluated using appropriate regression techniques, adjusting for site and in the case of QALYs, baseline utility.

Incremental cost-effectiveness ratios will be calculated if no arm is dominant, i.e. more effective and less costly than the other arm. Incremental net monetary benefit statistics will also be produced over a range of willingness to pay thresholds for a QALY.

Additionally, at 1 year, a cost consequence analysis from an NHS perspective will be used to compare the differences in costs and the differences in ICIQ-UI-SF.

Uncertainty for all analyses will be addressed using cost-effectiveness acceptability curves and sensitivity analyses. A health economics analysis plan (HEAP) will be produced prior to analysis, in which sensitivity analyses will be outlined. These are likely to include different approaches to dealing with missing data, based on reasons why the data might be missing.

#### QRI data analysis

Analysis of QRI data will be led by the qualitative research associate with the guidance of the QRI lead researcher, with a sample of transcripts independently coded by both researchers. QRI transcripts will be analysed thematically using constant comparative approaches derived from Grounded Theory methodology [28]. Audio-recorded recruitment appointments and follow-up discussions will be subjected to content, thematic and novel analytical approaches, including aspects of targeted conversation analysis and appointment timing (the ‘Q-QAT method’) [29, 30]. There will be a focus on aspects of information provision that are unclear, disrupted, or potentially detrimental to recruitment and/or adherence. Key issues identified from the observation notes of appointments and TMG/investigator meetings will be considered alongside other qualitative findings. Findings from all sources will be drawn together in a descriptive account that will be presented to the CI/TMG and will guide development of the recruitment intervention plan (QRI Phase II).

#### Interview Study analysis

Interview transcripts will be analysed by the qualitative researcher on an ongoing basis in an iterative manner, according to principles of thematic content analysis. Recordings will be listened to, and transcripts read and re-read for familiarisation. Segments of text will be ‘coded’ by assigning descriptive labels. Codes will be grouped on the basis of shared properties to create themes and coded transcripts will then be examined and compared to inductively refine and delineate themes (constant comparison). A subset of interviews will be independently analysed by a second study researcher and coding discrepancies discussed to maximise rigour and reliability. Plausibility of data interpretation will be further discussed between the study team throughout the analyses. Descriptive accounts of the audio-recordings and interviews will be prepared.

### Methods in analysis to handle protocol non-adherence and any statistical methods to handle missing data {20c}

The primary analyses will be based on the observed data and a sensitivity analysis will be conducted where missing data are imputed using appropriate methods based on patterns of missingness. Data will be entered promptly, and data validation and cleaning will be carried out throughout the trial. Where spurious data are observed, values will be checked against available records.

### Plans to give access to the full protocol, participant-level data and statistical code {31c}

The full study protocol is available online via the NIHR funding award records [31] and via a link in the study International Standard Randomised Controlled Trials Number (ISRCTN) registry [32], both of which are publicly accessible. The datasets analysed during the current study will be available to other researchers through a data sharing agreement (DSA) and the statistical code will be available from the corresponding author on reasonable request.

## Oversight and monitoring

### Composition of the coordinating centre and trial steering committee {5d}

#### Coordinating centre

The central trial team will be based within the BTC, a United Kingdom Clinical Research Collaboration (UKCRC)-registered clinical trials unit and will support the delivery and conduct of the trial. The CI will take overall responsibility for managing the various components of the trial and will meet at least monthly with the leads for each component. The CI will be supported by the Trial Manager who will take responsibility for the day-to-day management of the trial with the Trial Administrator and the lead Research Nurse. The data management team will oversee all IT aspects of the study.

#### Trial Management Group (TMG)

A TMG will meet at least once each quarter in the first 2 years, then 6 monthly to review progress, with ad hoc meetings, as required. The TMG will have responsibility for the day-to-day management of the trial and will report to the TSC. It will be chaired by the CI and will consist of relevant co-applicants, including a Patient and Public Involvement (PPI) co-applicant and representatives from the Sponsor and BTC.

#### Trial Steering Committee (TSC)

Membership, responsibilities and reporting mechanisms of the TSC are detailed in the TSC charter. The TSC will make key decisions and recommendations during the trial to the TMG and notified to the funder.

The TSC will comprise of an independent chair plus three additional independent members (a clinician, a statistician and an independently nominated PPI representative). The independent members will cover expertise in statistics, trials, urology and urogynecology. The CI will also be a formal (non-voting) member of the TSC. Observers may also attend (including other members of the TMG or members of other professional bodies) at the invitation of the Chair. The TSC will meet for the first time by month 6 of the trial and then 6 monthly thereafter.

### Composition of the data monitoring committee, its role and reporting structure {21a}

The DMC will monitor accumulating trial data for quality, completeness and patient safety and will make recommendations to the TSC regarding ethical or safety issues which may require a protocol amendment or closure of the trial. The DMC will comprise an independent chair, two other independent members with expertise in trials and statistics, and gynaecology and urology and the CI. Responsibilities and reporting mechanisms of the DMC are detailed in the DMC charter which has been developed using the DAMOCLES charter for independent DMCs [33]. The DMC will meet once prior to recruitment of the first participant and again during years 2, 3, 4 and 5 prior to the TSC meeting, to review the AE data and any other ethical aspects that arise and will report to the TSC.

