### Assignment of interventions: blinding

#### Who will be blinded {17a}

Due to the nature of the interventions, participants and those administering the interventions will not be blinded to group allocation nor will the supporting clinical and site staff, to ensure relevant data collection. Two statisticians based at the UOB will support this trial. The senior statistician co-applicant will be blinded throughout the trial. The second trial statistician will perform all disaggregated analyses according to a pre-specified statistical analysis plan (SAP) and will attend closed Data Monitoring Committee (DMC) meetings as required. The health economist(s) will be blinded when cleaning data, but unblinded when conducting the analysis. Other members of the study team will remain blinded to aggregate data. The Study Manager and administrative staff will likely be unblinded to individual-level data to enable appropriate data collection.

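### The Chief Investigator is listed as a full member of the Data Monitoring Committee, which contradicts the protocol's independent DMC and leaves access to by-arm data unexcluded

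*Protocol article*

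**What the plan says.** On membership, the protocol article (Composition of the data monitoring committee, its role and reporting structure {21a}) states: "The DMC will comprise an independent chair, two other independent members with expertise in trials and statistics, and gynaecology and urology and the CI". It leaves responsibilities and reporting to a DMC charter, modelled on one written for independent committees. Meetings are scheduled once before the first participant is recruited and again in years 2, 3, 4 and 5, to look at adverse events and ethical matters.

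On independence, Interim analyses {21b} states: "An independent DMC will review confidential accumulating data at its discretion, but at least annually". It adds: "No interim statistical analyses by study arm are planned".

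On blinding, Who will be blinded {17a} gives all disaggregated analyses to the second trial statistician, under a pre-specified analysis plan. It says that this statistician "will attend closed Data Monitoring Committee (DMC) meetings as required". For everyone else not named there it says: "Other members of the study team will remain blinded to aggregate data". Procedure for unblinding if needed {17b} then says that the senior statistician alone stays blinded throughout.

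On the CI's other roles, the coordinating centre section gives the CI overall responsibility for managing the trial. Of the Trial Management Group (TMG) it is said: "It will be chaired by the CI". On the Trial Steering Committee (TSC): "The CI will also be a formal (non-voting) member of the TSC".

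**The concern.** A DMC can look at accumulating data by arm without biasing the trial because its members do not run the trial. The membership sentence gives a seat to the person who does. The seat is unqualified, whereas the CI's seat on the TSC is expressly non-voting.

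This trial has several routes by which knowledge of emerging results could affect conduct. Participants and treating staff know the allocation, and the primary outcome (ICIQ-UI-SF at 1 year) is patient-reported. The rule against crossing over before 1 year is guidance that cannot be enforced. The CI works with the qualitative team on the plan to improve recruitment and chairs the group that manages the trial day to day. If the CI saw results by arm during recruitment or follow-up, advice to sites could shift without anyone intending it. That is operational bias, and it could not be removed at the analysis stage.

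**Working it through.** No arithmetic bears on this point beyond a headcount, and no figure in the plan depends on it. The check is a comparison of the protocol's own statements.

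1. **Composition.** One independent chair + two other independent members + the CI = 4 members. Independent: 3 of 4 (75%). Not independent: 1 of 4 (25%). The sentence defines who makes up the committee, so the CI is a member and not an invited attendee.

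2. **Composition against the claim of independence.** {21b} calls the committee independent without qualification. {21a} includes the trial's lead. Both cannot be right as written. This contradiction is direct and needs no assumption about who attends which session.

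3. **Composition against blinding.** {17a} keeps the other study team members blinded to aggregate data and makes no exception for the CI. I read aggregate data there as summaries by arm. A DMC member would ordinarily see what the committee reviews, which {21b} describes as confidential accumulating data. The two sections conflict if membership carries access to closed sessions. They are compatible only if the CI is kept out of those sessions, and no section says so. {17b} does not help: by naming the senior statistician as the only person blinded throughout, it leaves the CI's status unclear.

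4. **Would by-arm data exist for the committee to see?** {21b} plans no interim statistical analysis by arm. {17a} nevertheless foresees disaggregated analyses and closed DMC meetings attended by the statistician who performs them. Adverse events are on the DMC's agenda and, with re-treatment, are secondary outcomes. By-arm safety tables are therefore possible even without a planned interim test.

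5. **Is the CI placed in, or kept out of, closed sessions?** No section does either.

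6. **Timing.** Recruitment began in January 2020 and is expected to end around January 2024 (Trial status). If the DMC's years are counted from January 2020, which is an assumption, years 2, 3 and 4 are 2021, 2022 and 2023. Three of the four later scheduled meetings would then fall within recruitment. All follow-up is to be analysed together, so on the same dates the last 3-year data would arrive around January 2024 + 3 years = January 2027, after all of those meetings.

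**The case against.** The strongest reply is that the protocol already contains the safeguards. It provides for closed meetings, keeps the study team blinded to aggregate data, plans no interim analysis by arm, and limits the scheduled meetings to adverse events and ethical matters. Three of four members, including the chair, are independent. Recommendations go to a TSC with an independent chair and three further independent members, on which the CI has no vote. Session attendance is normally set out in a charter, which is not shown, and an article's silence on it is no fault.

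Much of this stands, and it limits what can be said. A reader might infer that trial leadership is exposed to by-arm results. The documents do not say that: nothing places the CI in a closed session. A reader might also infer that the CI, as a member of a body that agrees the analysis plan, could shape that plan after seeing results. This is at most a secondary risk, since {17a} ties disaggregated analyses to a plan specified beforehand and the subgroups must be agreed in advance. Nor do the documents show that the CI approves important decisions: the TSC and the sponsor approve important amendments. With three independent members and an independent TSC, they also give no ground for saying that any DMC recommendation is undermined. Finally, the CI's review of reportable serious adverse events is legitimate case-by-case safety work and is not the issue here.

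What the reply does not remove is the membership sentence itself. The point is not that attendance rules are missing. The article publishes a composition that conflicts with its own description of the committee, and a charter the reader cannot see does not change that.

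**Conclusion.** The point holds as an internal contradiction with an open risk attached. The certain part is that {21a} makes the CI one of four DMC members without any limit, against the independent committee of {21b}. The conditional part is the conflict with {17a}, which arises if membership includes closed sessions. Exposure of the CI to by-arm data is neither stated nor excluded.

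The size cannot be expressed as an error rate or a loss of power. It is one seat in four, across four scheduled meetings after the trial opens, of which three would fall during recruitment if years run from January 2020. The conclusion rests on reading the membership sentence at face value and on reading aggregate data in {17a} as summaries by arm. It would be answered in substance if the charter confines the CI to open sessions, but the article's text would still need correcting.

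**What to change.** In {21a}, delete the CI from the list of DMC members. Add that the CI may attend open sessions only, by invitation, without a vote and without access to data by arm, and that such data go only to the independent members and the unblinded statistician in closed session.

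Align the related text: {17a} should say that the CI is among those blinded to by-arm summaries; {17b} should no longer imply that only the senior statistician is blinded; {21b} can keep its description of an independent committee once {21a} supports it; and the charter should match. Because recruitment started in January 2020 and meetings may already have taken place, a short file note of which sessions the CI attended would settle the matter for the period so far.

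The cost is a few lines in the protocol and charter. Sample size, data collection and analysis are unaffected.

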### Adverse event reporting and harms {22}

AE data are collected and assessed throughout an individual’s participation in the study as secondary outcomes. The PI at each participating site (or appropriate delegate) is responsible for categorising whether AEs are serious, expected and related. Serious and non-serious adverse events (S/AEs), reported by the participant or research teams, will be recorded, and reported in accordance with the Good Clinical Practice (GCP) guidelines and the Sponsor’s Research Related Adverse Event Reporting Policy.

#### Adverse event (AE)

An AE includes any untoward medical occurrence in a study participant administered an intervention which does not necessarily have a causal relationship with this treatment. In all instances, it will be up to the Principal Investigator (PI) of each participating site (or appropriate delegate) to determine whether the person’s change in health is related to the trial. AEs are not continuous and persistent disease or symptoms, present before the trial, which fail to progress, signs or symptoms of recurrent SUI or treatment failure.

#### Serious adverse event (SAE)

A SAE is any untoward medical occurrence that:Results in deathIs life-threateningRequires inpatient hospitalisation or prolongation of existing hospitalisationResults in persistent or significant disability or incapacityConsists of a congenital anomaly or birth defect.

Important AEs that are not immediately life-threatening or do not result in death or hospitalisation but may jeopardise the participant or may require intervention to prevent one of the other outcomes listed in the definitions above, will also be considered serious. Medical judgement will be exercised in deciding whether an AE is serious in other situations.

#### Expected events

Due to the nature of the treatments for recurrent SUI, AEs are expected to occur throughout the course of the trial. Events that can be expected during/after any surgery, or within this patient population are listed below.Anaesthetic complications, e.g. stroke or cardiac events such as myocardial infarctionOperative injury to adjacent structureFistulaReturn to theatreITU admissionNew urinary tract symptomsUrinary tract infectionWound infectionPelvic organ prolapse (POP)Urinary retention/catheterisation (intermittent self-catherisation (ISC) and indwelling)PainImplant exposure (tape, AUS)Incisional herniaDeep vein thrombosis (DVT)/Pulmonary embolism (PE)Bleeding/haematoma/blood transfusionChest infectionNew sexual problems e.g. dyspareuniaOther infections (sepsis, septicaemia, abscess, respiratory)Inflammation, e.g. osteitis pubisDeath

#### Reporting procedures

All adverse events (serious and non-serious) will be recorded in the participant’s medical notes and appropriate study CRF. SAEs will also be recorded in a study-specific SAE log which will be regularly reviewed by the DMC and Sponsor.Non-fatal expected SAEs and unexpected SAEs which are not causally related to the research procedures will not be reported to the Sponsor.Fatal expected SAEs and unexpected SAEs which are causally related to the research procedures (serious adverse reactions, SARs) will be reported to the study Sponsor within 24 h of staff becoming aware of the event. SARs will also be reported to the REC immediately.

The PI (or trained delegate) at each study site is responsible for identifying and categorising AEs, ensuring all SAEs are documented, reported and followed up appropriately. The CI is responsible for clinical oversight of the safety of patients participating in the trial including an ongoing review of the risk/benefit, categorising AEs where it has not been possible to obtain local medical assessment, reviewing all reportable SAEs and ensuring appropriate reporting of SAEs.

